### **Statistical Analysis**

Descriptive statistics will be calculated as frequencies and percent. The comparison between test and control sub-groups will be done using Chi-squared test. Logistic regression analysis will be conducted to assess the effect of the groups (based on IQ level), subgroups (test or control) and confounders (fear, gender, and age) on the outcome (behavior dichotomies into positive and negative behaviors). Statistical analysis will be done using SPSS version 17.0 (SPSS Inc., Chicago, Ill., USA). Significance level will be set at 5 %.

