### **Aim of the study**

This study will be conducted to investigate the effect of parental active/ passive presence technique on the overall behavior of preschool children with different levels of intelligence and fear.

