### **Study Sample**

#### ***Sample size estimation***

Sample size was based on assuming 5% alpha error, 20% beta error, allocation ratio between test and control subgroups of 1:1, and probability of positive behavior in the control subgroup of low intelligence quotient (IQ) = 0.25.  An estimation was made of the probability of positive behavior in the test subgroup with low IQ to have positive behavior as healthy children = 0.87.  So, to detect the difference between control and test groups, it was calculated that 9 children per subgroup would be needed.  To ensure adequate power, we estimated a reduction in the difference between test and control groups regarding probabilities of positive behavior of 50% with calculated required number= 24. This was increased to 25 children per subgroup to account for non-completion. Thus, the total required number of children= number of groups X number of subgroups X number per group= 3 X 2 X 25= 150 children.

Visual Screening and parent meeting will be carried out to identify children who will fulfill the inclusion criteria.

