### **Randomization and allocation concealment**

Children will be stratified based on their IQ into 3 groups: high, average, and low IQ groups. In each group, children will be randomly and equally allocated according to intervention into test and control sub-groups. The study will thus include

6 subgroups. Randomization will be performed by a trial independent person using computer random number generator. Randomization sequence in blocks of 2 will be created using random allocation software version 1.0.0. The allocated group will be written on piece of paper which will be folded and enclosed in a sealed envelope carrying the child's name on its cover. At the time of intervention, an assistant will open the envelope, identify the sub-group to which the child will be assigned.

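### The logistic model names no arm-by-IQ or arm-by-fear term: no stated analysis tests whether the effect of active presence differs by IQ, and none examines it by fear level

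*Protocol*

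**What the plan says.** - **Aim of the study:** the trial is to "investigate the effect of parental active/ passive presence technique on the overall behavior of preschool children with different levels of intelligence and fear". The title and the null hypothesis use the same frame, and the PICO question under Study Design puts fear and intelligence levels into the population.
- **Randomization and allocation concealment:** "Children will be stratified based on their IQ into 3 groups: high, average, and low IQ groups", with test and control sub-groups randomised inside each, six sub-groups in all. Fear is not a stratification factor.
- **Sample size estimation:** rates are given for the low-IQ group only, and the per-sub-group number is multiplied by 3 x 2 to reach 150.
- **Second visit:** fear is scored on the Facial Image Scale (FIS) before allocation. Outcome assessment groups the score as low (1-2), moderate (3) and high (4-5).
- **Statistical Analysis:** a chi-squared test compares test and control sub-groups, and a logistic regression is to "assess the effect of the groups (based on IQ level), subgroups (test or control) and confounders (fear, gender, and age) on the outcome". No product term and no comparison of arm effects between levels is mentioned.

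**The concern.** A logistic model containing only the listed terms returns one arm odds ratio, assumed equal at every IQ and fear level, plus the prognostic effects of IQ, fear, gender and age. It cannot show whether active presence works better at one level than at another.

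For IQ, the chi-squared tests fill part of the gap, because the sub-groups they compare are nested in IQ groups. What is missing is a comparison of those effects with each other. Without one, a significant result in low IQ beside a non-significant result in high IQ invites the conclusion that the technique works differently, which neither test supports.

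For fear there is nothing: it enters only as an adjustment term, so the fear part of the framing would go unanswered.

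**Working it through.** **1. The plan's own figures.** Inputs from Sample size estimation: "Sample size was based on assuming 5% alpha error, 20% beta error, allocation ratio between test and control subgroups of 1:1"; control rate 0.25 and test rate 0.87, both for low IQ. Two-sided testing is assumed, since the protocol does not state it. With p̄ the mean of the two rates,

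n = [1.96√(2p̄(1−p̄)) + 0.842√(p₁q₁ + p₂q₂)]² / (p₁ − p₂)².

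- 0.25 vs 0.87: n = 8.8, so 9, which reproduces the stated 9 per sub-group.
- Half the difference (0.62/2 = 0.31), so 0.25 vs 0.56: n = 38.2, so 39. The stated 24 is not reproduced. That is a separate matter; below I use the 25 per sub-group that the protocol plans.

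**2. What the chi-squared test within low IQ can do.** For 0.25 vs 0.56 with 25 per sub-group: (0.31 × √25 − 1.96√0.482)/√0.434 = (1.55 − 1.361)/0.659 = 0.287, so power is about 61%. Direct calculation from the binomial distributions gives about 65%.

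**3. Interaction, one pair of IQ groups (1 df, Wald).** Suppose low IQ moves from 0.25 to 0.56 and another group stays at 0.50 in both arms (an assumption).

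- Low-IQ log odds ratio: ln(0.56/0.44) − ln(0.25/0.75) = 1.340, an odds ratio of 3.82.
- Variance of each cell's log odds: 1/(25pq), giving 0.213, 0.162, 0.160 and 0.160. Sum 0.696, SE 0.834.
- z = 1.340/0.834 = 1.61; power = Φ(1.61 − 1.96), about 36%. With the other group at 0.25 or 0.70 it is 32% or 34%.

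At exactly these rates the low-IQ odds ratio would be 3.82 (95% CI 1.15 to 12.7, from SE √0.376 = 0.613), and the other group's would be 1.00 (0.33 to 3.03, from SE √0.320 = 0.566). One is significant and the other is not. Yet their ratio is exp(1.340 ± 1.96 × 0.834), that is 3.82 with CI 0.74 to 19.6, so a difference is not established.

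**4. Interaction over three IQ groups (2 df, likelihood ratio).** Simulation of 3,000 trials per scenario, 25 per cell, IQ and arm only. Fear, gender and age were not simulated.

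| Low IQ | Average and high IQ, no effect (assumed rates) | Arm x IQ test | Common arm term |
|---|---|---|---|
| 0.25 to 0.56 | 0.25 and 0.25 | 34% | 29% |
| 0.25 to 0.56 | 0.50 and 0.70 | 38% | 25% |
| 0.25 to 0.87 | 0.25 and 0.25 | 93% | 82% |

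**5. Fear.** The protocol gives no fear distribution and no behaviour rates by fear level, so no power can be computed for arm x fear.

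**6. The role of fear.** Because it is measured before allocation, fear cannot confound the arm comparison other than by chance imbalance. For that comparison it is a baseline covariate and a possible effect modifier.

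**The case against.** Four points can be made for the plan.

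- **The wording does not exclude interactions.** It lists factors whose effect will be assessed, and a statistical analysis plan that is not shown could add product terms. That the model has main effects only is therefore an inference. It stands as a caution, but the protocol does fix a list of terms and gives fear the role of a confounder, and neither matches the aim as framed.
- **Effect modification is not stated as the question.** No section speaks of effects that differ by level. The PICO question uses fear and IQ to describe the population, and the Introduction gives intelligence and parental presence as two separate gaps. So it cannot be called the trial's sole question. The average effect is part of it too.
- **A benefit in one IQ group is not simply averaged away.** A reader might infer this from the common odds ratio. The documents do not support it: the natural reading of the chi-squared plan gives a comparison within each IQ group, and at 61-65% power for the halved effect it does better than the common arm term (25-29%) or the interaction test (34-38%).
- **The confounder label changes no coefficient.** This is true, and adjustment for fear is relevant when the non-randomised IQ groups are compared with each other. The point is about interpretation of the arm comparison.

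What remains is that separate tests do not test a difference between IQ groups, and that fear has no arm-by-level analysis at all.

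**Conclusion.** The concern holds in limited form. As listed, the analyses give an average arm effect and, through the chi-squared tests, arm comparisons within IQ groups. They give no test of whether the effect differs by IQ and nothing on the effect by fear level. The randomised average comparison is not invalidated, so this is a worthwhile, inexpensive improvement and not an error that undermines the trial.

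The size rests on assumptions. The protocol gives rates for low IQ only, and with those of the other groups assumed, the 2-df arm x IQ test has about 34-39% power if only low IQ moves from 0.25 to 0.56.

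A more dramatic case can be built: with low IQ 0.25 to 0.56, average 0.40 in both arms and high IQ 0.56 to 0.25, the common arm term rejects in about 5% of trials and the interaction test in about 84%. That needs active presence to worsen behaviour in high-IQ children, which nothing in the protocol suggests, so it should not be taken as the expected consequence of the plan.

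**What to change.** 1. Keep the adjusted average arm effect and the within-IQ comparisons.
2. Pre-specify, as an additional analysis, arm x IQ group (2 df) and arm x fear. Choose one fear coding beforehand: either the FIS score as a trend (1 df) or the protocol's low/moderate/high grouping (2 df).
3. Report arm odds ratios with 95% confidence intervals for each IQ group and each fear level, beside the interaction tests.
4. State that a difference between levels will not be inferred from significance in one and not in another.
5. Describe fear, gender and age as baseline covariates for the arm comparison.

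The cost is analysis wording and modest analysis work; no further children, visits or measurements are needed. The downside is low interaction power and possibly sparse fear levels, since fear is not stratified. The results should be presented as estimates with intervals, and a non-significant interaction should not be read as evidence of equal effects.

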A study of children's individual characteristics including age, sex, intelligence quotient and personality variables may help in the understanding of their dental fear. Rud and Kisling (1973) investigated the influence of mental development on children acceptance of dental treatment, by using Banit's, Cattells's, and Leiter's methods on 108 individuals with age of (3-9 years). They reported that children with lower IQs showed more fearful behavior. Savin, and Maxim (2008) carried out a study on 88 subjects (54 girls and 34 boys) aged between 6-8 years old: They divided them into 64 normal subjects from psycho-mental viewpoint and 24 subjects with audio sensory disabilities. They made a complex assortment of investigations: projective draw test (thematic projective test), Raven's progressive matrix test and a questionnaire. The results of all the tests showed that there was a significant correlation between the

IQ level and the behavioral conduct manifested by the child. The subjects with higher IQ level presented a normal conduct. 

Communicative management is an ongoing subjective process that becomes an extension of the personality of the dentist. Associated with this process are the specific techniques of Tell Show-Do technique, Parental presence/absence,  and others.  Parents exert a significant influence on their child's behavior, especially if they have had previous negative dental experiences.  The presence or absence of the parent sometimes can be used to gain cooperation for treatment.  Parents' insistence to be present during their child's treatment does not mean they intellectually distrust the dentist. It might mean they are uncomfortable if they visually cannot verify their child's safety. Therefore, parental presence should not cause any conflict within the dentist. On the other hand, parental presence could be used actively or passively to during dental treatment. 

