It is evident that a strong relationship exists between dental fear and children's behavior.  However, limited research has dealt with the effect of children's intelligence on their fear and consequently on their behavior in the dental clinic.  In addition, no research has investigated active versus passive presence of parents in the dental operatory and its effect on the child's behavior. These problems have furnished the stimulus for the present investigation.

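### The single logistic model enters fear as a confounder of the IQ effect although the rationale places fear between IQ and behaviour, so the IQ coefficient omits whatever part runs through fear

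*Protocol*

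**What the plan says.** The Statistical Analysis section of the protocol specifies one logistic regression, to "assess the effect of the groups (based on IQ level), subgroups (test or control) and confounders (fear, gender, and age"). The covariates and the outcome are given together as "confounders (fear, gender, and age) on the outcome (behavior dichotomies into positive and negative behaviors"). The effect of IQ group is thus one of the quantities that the model is meant to deliver, and fear is in the same model under the label of confounder.

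The Introduction & Literature review describes how these variables relate:

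- It names as under-researched the "effect of children's intelligence on their fear and consequently on their behavior in the dental clinic", and counts this among the problems that prompted the study.
- On a cited study of mental development and acceptance of dental treatment it says: "They reported that children with lower IQs showed more fearful behavior".
- It regards it as evident that "a strong relationship exists between dental fear and" behaviour.
- On another cited study, without reference to fear, it says: "The subjects with higher IQ level presented a normal conduct".

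IQ is tested at the first visit. Fear is scored on the Facial Image Scale (FIS) at the start of the second visit, before random allocation (Second visit).

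**The concern.** A confounder of the IQ effect would have to influence IQ, or share a cause with it, as well as influence behaviour. The Introduction instead puts fear after IQ and before behaviour. Holding a variable in that position constant does not remove confounding from the IQ effect. It removes the part of the effect that travels through that variable.

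The risk is one of interpretation. A fear-adjusted IQ odds ratio near 1 could be reported as showing that intelligence has little bearing on behaviour, when the model had set aside one of the routes that the Introduction describes. The label in the analysis section encourages this misreading: a reader who takes fear for a confounder will take the adjusted coefficient for the better estimate of the whole IQ effect.

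**Working it through.** The protocol gives no figure for fear by IQ group, for the strength of fear on behaviour, or for an IQ effect. There is therefore no stated result to reproduce, and every numerical input below is an assumption chosen to show a range.

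**Step 1. The passages side by side.** Introduction: IQ, then fear, then behaviour. Second visit: fear is measured after IQ and before allocation. Statistical Analysis: IQ effect and fear in one model, fear called a confounder. For the arm comparison, fear is a pre-allocation covariate and adjustment is sound. For the IQ comparison, it lies on the route that the Introduction proposes.

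**Step 2. IQ acting only through fear.** Assumptions:

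- high fear in a proportion *a* of low-IQ children (0.4, 0.5 or 0.6) and in 0.2 of high-IQ children;
- probability of positive behaviour 0.30 for a low-IQ child with high fear;
- odds ratio *F* of 3, 5 or 8 for not having high fear;
- direct IQ odds ratio *D* = 1.

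Marginal probability in an IQ group = P(high fear) × p(high fear) + P(not high fear) × p(not high fear).

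Example with *a* = 0.5 and *F* = 5:

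- odds with high fear = 0.30/0.70 = 0.4286; odds without = 5 × 0.4286 = 2.143, so p = 0.6818;
- low IQ: 0.5 × 0.30 + 0.5 × 0.6818 = 0.4909;
- high IQ: 0.2 × 0.30 + 0.8 × 0.6818 = 0.6055;
- total odds ratio = (0.6055/0.3945)/(0.4909/0.5091) = 1.59; fear-adjusted odds ratio = 1.00.

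Over the nine combinations the total odds ratio runs from 1.23 (*a* = 0.4, *F* = 3) to 2.21 (*a* = 0.6, *F* = 8). The adjusted one is 1.00 each time.

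**Step 3. A direct effect as well, *D* = 1.5.** Same example:

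- high-IQ odds with high fear = 0.4286 × 1.5 = 0.6429, p = 0.3913; without = 2.143 × 1.5 = 3.214, p = 0.7627;
- high IQ: 0.2 × 0.3913 + 0.8 × 0.7627 = 0.6884;
- total odds ratio = (0.6884/0.3116)/(0.4909/0.5091) = 2.29; adjusted = 1.50;
- share of the log odds ratio omitted = 1 − ln 1.5/ln 2.29 = 0.51.

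Over the nine combinations the total is 1.82 to 3.09 and the share omitted is 32% to 64%.

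**Step 4. No link between IQ and fear.** Put high fear at 0.2 in both groups, with *F* = 8 and *D* = 1.5:

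- without high fear, low-IQ odds = 8 × 0.4286 = 3.429, p = 0.7742; high-IQ odds = 1.5 × 3.429 = 5.143, p = 0.8372;
- low IQ: 0.2 × 0.30 + 0.8 × 0.7742 = 0.6794;
- high IQ: 0.2 × 0.3913 + 0.8 × 0.8372 = 0.7480;
- total odds ratio = (0.7480/0.2520)/(0.6794/0.3206) = 1.40; adjusted = 1.50.

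Here the adjusted value is further from 1. Nothing is mediated; the gap arises because odds ratios are non-collapsible.

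**Step 5. Three levels of IQ and of fear.** Population-level logistic fits with weak, mid and strong assumed IQ–fear links, high versus low IQ, gave the same pattern:

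| Assumed situation | Total OR | Fear-adjusted OR |
|---|---|---|
| Through fear only, all links and fear effects tried | 1.10 to 9.35 | 1.00 |
| Mid link plus direct effect | 2.70 | 1.65 |
| Mid link plus larger direct effect | 4.19 | 2.72 |
| Weak link, very strong fear effect | 2.54 | 2.72 |
| Weak link, large direct effect | 6.41 | 7.39 |

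With a mid or strong link the adjusted value was nearer 1 in every case. With a weak link it could go either way.

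**The case against.** The strongest reply is that this concerns a secondary quantity. The Hypothesis, the Aim of the study and the PICO question under Study Design are about the parental-presence technique; none states a hypothesis on IQ itself. The IQ–fear–behaviour chain is one of two gaps that the Introduction names, and the other is the randomised question. All of this stands. A reader might infer that the trial would end up contradicting its own hypothesis, or that its main result is compromised. The documents support neither.

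Second, the protocol does not say whether a total or a direct IQ effect is wanted, and a model with fear can estimate a direct effect if fear and behaviour share no unmeasured cause. This also stands, so the coefficient is not wrong for every purpose. But the protocol does not call it a direct effect, the label of confounder points the other way, and no stated model gives the total effect.

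Third, a reader might infer that the IQ effect is always biased toward none. Steps 4 and 5 show that this is not so. Nor does the Introduction argue that IQ acts wholly or mainly through fear: it gives no share, and it also cites a link between IQ and conduct without mention of fear. The study of lower-IQ children may describe chairside behaviour rather than self-reported fear before treatment.

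Fourth, precision is limited in any case. There are 50 children per IQ group (2 × 25, Sample size estimation). For 0.4909 versus 0.6055 the standard error is √[(0.4909 × 0.5091 + 0.6055 × 0.3945)/50] = 0.0989, so z = 0.1146/0.0989 = 1.16 and power at two-sided 5% is about 21%. At the top of the fear-only range (0.49 versus 0.68) it is about 50%. Dropping fear would often still leave a non-significant IQ result. This limits how much a significance verdict depends on the adjustment; it does not change what the coefficient means.

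Finally, the absence of a table of fear by IQ group is not a fault, since such tables are commonly left to a statistical analysis plan.

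**Conclusion.** The point holds in a limited form. On the protocol's own rationale fear is a possible mediator of the IQ effect, and calling it a confounder in the model that is to assess IQ is inconsistent with that rationale. The planned IQ coefficient omits whatever runs through fear. If the IQ–fear link is substantial, the coefficient will usually lie closer to none than the total effect does. It is 1.00 if fear is the only route, and 32% to 64% of the log odds ratio is omitted in the mixed cases of step 3.

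These sizes rest on assumed prevalences and odds ratios. They also assume that fear as coded in the model captures the pathway and that fear and behaviour have no unmeasured common cause. The real size is unknown. IQ is not randomised, so even the total effect is an observational estimate.

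The comparison of active with passive parental presence is untouched: fear is measured before allocation and is a sound baseline covariate for it.

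**What to change.** In the Statistical Analysis section:

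- Report the IQ-group effect from a logistic model with arm, age and gender but without fear, and call it the total effect.
- Keep the model that includes fear for the arm effect. Label its IQ coefficient a direct effect, and state that this reading assumes no unmeasured common cause of fear and behaviour.
- Describe fear as a baseline covariate for the arm comparison and a possible mediator of IQ, not as a confounder of IQ.

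A table of FIS category by IQ group would be a useful supplement, as it would show whether the first link of the proposed chain is present in these children.

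The cost is one further model on data already collected and a change of wording. The randomised analysis and the sample size stay as they are.

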### **Funding**

There will be no funding to support this study.

### **Problems anticipated**

- 1- Difficulties in recruiting equal number of participants in each IQ group.
- 2- Drop out of participants in the second visit.

**Estimated duration:** 12 months.

| Tasks                                  | Months |   |   |   |   |   |   |   |   |    |    |    |
|----------------------------------------|--------|---|---|---|---|---|---|---|---|----|----|----|
| Beginning- end of study                | 1      | 2 | 3 | 4 | 5 | 6 | 7 | 8 | 9 | 10 | 11 | 12 |
| Proposal writing                       | X      |   |   |   |   |   |   |   |   |    |    |    |
| Training course                        |        | X |   |   |   |   |   |   |   |    |    |    |
| Purchase of preventive materials       |        | X |   |   |   |   |   |   |   |    |    |    |
| Subjects' recruitment                  |        | X | X | X | X | X | X |   |   |    |    |    |
| Intervention application               |        |   |   |   |   |   |   | X | X | X  |    |    |
| Data management & statistical analysis |        |   |   |   |   |   |   |   |   |    | X  | X  |

